#### Expected Outcome

We expect LC-NE functioning to provide added predictive validity, with an increase in explained variance compared to previous psychopathology, childhood adversity, and cognitive ability. We assume a moderate accuracy of the normative model and substantial associations of normative range deviations with transdiagnostic psychopathology. We further expect that the spatial direction of the range deviation within the normative model differentiates the factors of transdiagnostic psychopathology. The simplicity of the model emphasizes its feasibility for use in clinical settings. The final task of LOCUS-MENTAL will provide a tool for quantitative risk prediction in at-risk populations of preschoolers.

#### Risk Assessment

We acknowledge that LC-NE functioning is not the only determinant in the complex development of psychopathology, but given this, the time is ripe to test a promising neurophysiological mechanism as an objective predictor that improves the assessment of clinical risk over the current practice of subjective evaluation.

### Ethical Considerations

The study was approved by the Ethical Committee (reference number: 2024‐2160) and the Data Protection Officer of the Medical Faculty of Goethe University Frankfurt. To date, no adverse events have been reported by any comparable study, and thus we expect no risks nor harm to our participants. The study is planned and will be conducted and analyzed according to Good Scientific Practice (GSP) guidelines, the Declaration of Helsinki, and the European Data Protection Directive (DSGVO). Study participation is on a voluntary basis, and participants can withdraw from study participation at any time without any adverse consequences concerning their medical or psychiatric treatment in our clinic. Participants will also receive monetary compensation for their time. All relevant information regarding data protection and the voluntary basis of participation will be communicated to participants and their legal caregivers verbally, as well as in the form of written informed consent forms. We also obtain verbal assent from the preschool participants. The child’s right to withdraw at any time will be prioritized over parental consent. During assessments, the child will be closely monitored by the experimenter that is present at all times, and signs of acute distress (such as crying, physical withdrawal, or verbal expression of a desire to stop) will lead to termination of the assessment. In cases of suspected or disclosed adversity, the research team will inform the principal investigator immediately (licensed psychotherapist for children), who offers a voluntary counseling appointment to discuss potential adversity with the family and the child. In line with German child protection laws and in accordance with our clinical guidelines, the quantity and quality of suspected adversity might result in further support by our department or even a report to authorities (eg, imminent danger of ongoing adversity). We acknowledge that the development of a risk assessment tool could potentially lead to stigmatization and misuse. With our data management plan outlined below, we made sure that individual risk prediction cannot be associated with personally identifiable information. We further refrain from any nonscientific use of the prognostic risk marker. The rights to the information of prognostic risk remain with the participants in accordance with DSGVO. We are confident that a prognostic risk marker also provides the opportunity to shift from a health care system that focuses on intervention after manifestation of psychopathology to a focus on targeted prevention. Children at an elevated risk for mental health problems as identified by LOCUS-MENTAL could receive further case management at our outpatient clinic, where we decide on useful next steps on a case-by-case basis with evidence-based treatments. For example, caregivers of children at risk could be offered the opportunity to receive parent trainings that are established in the treatment of mental health problems in children. This may aid in the early prevention of the initial manifestation of psychopathology. Our newly established outpatient clinic for early detection could be the ideal environment to use risk assessment information for positive clinical outcomes.

LOCUS-MENTAL applies a noninvasive neuroimaging methodology that allows indexing neuronal activity by video-based pupillometry. Previous work showed feasibility and established this methodology in clinical samples of children. In addition, we apply further noninvasive assessments with electroencephalography. These measures introduce a burden for the participants and can induce a state of irritability but do no harm. This also applies to the application of an age-appropriate social stress test. The test induces a temporary impression that the child’s performance was insufficient in a task, which has been associated with a cortisol release response that needs to be quantified to achieve the objective of task 3.2. The social stress test thus includes a comprehensive disclosure strategy after the test to alleviate any negative effects. In task 3.2, we further collect tissue as hair samples (cutting off hair strands) and saliva samples (chewing an artificial fiber). These methods of tissue collection are also entirely non-invasive. The tissue samples will be processed by experienced contractors and subsequently destroyed. In the project, we further assess personally identifiable information that is handled according to the descriptions in section 2.4. We expect that this study does not involve an immediate risk of yielding knowledge, products, or technology that could intentionally be misused to cause substantial harm.

Questionnaire and interview data will be collected via our on-premises online tool according to the European General Data Protection Regulation (GDPR). We further do video-based eye tracking, apply EEG, and collect biological samples. Hair samples will be analyzed by Dresden Labservice with online solid-phase extraction in liquid chromatography-tandem mass spectrometry. Saliva samples will be analyzed by Daacro Contract Research with the ELISA Salimetrics Assay in a double estimation. Metadata will be generated by a printed case report form. Data are transferred to electronic databases that allow for automated quality controls and sanity checks. Eye tracking and EEG data will also receive quality control by peer-reviewed preprocessing pipelines. We established standard operating procedures to document research data, personnel will be trained in GSP, and all data handling will be in accordance with the GDPR. We differentiate between person-identifying information and research data that are separated in different networks, both behind the clinic’s firewall. The data can only be combined by a person identification code that is restricted in access to authorized personnel and stored on the clinical network. This is separated from a pseudonymized research network. All databases run on a Microsoft Access front- and back-end with an Active Directory system. Data are stored on on-premises servers with backups in a different building. After the project’s end, anonymized research data will be made available according to Open Science standards and archived for 10 years. The author (IT) will administer the project-specific databases. PhD students will have read and write rights with log protocols. A dedicated database manager with a permanent position is the administrator of all databases.

The LOCUS-MENTAL study uses targeted strategies across its work packages to manage missing data and ensure robust longitudinal findings. Work package 1 focuses on feasibility measures by using passive and child-friendly paradigms to achieve a projected completion rate of over 80%. Statistical analysis will exclude children that have per-task data validity rates of less than 50% or more than one missing task. The auditory oddball task is a marker task that is required to be included in the statistical analysis. We established standardized procedures of pupillometry data preprocessing to address within-trial missing data due to inattention. Work package 2 addresses high-burden EEG assessments by designating them as “more optional” in the context of the overall project, which allows for an expected 30% attrition rate without hindering subsequent study objectives. For the longitudinal assessments in work package 3, the study implements retention strategies like online data collection and locator documents. In addition, the statistical framework of work package 3 includes LMM and structural equation modeling to handle intermittent missingness across time points. Questionnaire data on an item level with per-measure missing rates up to 20% will be addressed by Multiple Imputation by Chained Equations (MICE) that preserves statistical power under the missing at random assumptions. However, children with increased irritability or increased burden may be more likely to drop out (ie, missing not at random or MNAR). Thus, pattern mixture models will be applied as a sensitivity analysis to determine if the developmental trajectories of LC-NE functioning are biased by specific attrition patterns. In addition, Inverse Probability Weighting (IPW) in the longitudinal data analysis can be used to adjust for non-random attrition by weighting the remaining participants based on baseline characteristics (eg, socioeconomic status or initial psychopathology scores) that predict dropout. Missing bio samples will be addressed by case-wise exclusion in the specific subanalysis. Finally, work package 4 uses v-fold validation to evaluate the predictive stability of the risk prediction tool.

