#### Sample Size and Power

A power analysis using a linear mixed model (LMM) indicates a power of *β*=.82 for 90 participants to detect a moderate stimulus effect (b=0.3) in the auditory oddball task (100 trials, 20% oddballs).

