#### Battery Design

##### Overview

The battery consists of 4 individual tasks. The primary task is a passive auditory oddball task, and the 3 additional tasks are a rapid sound sequence, a visual oddball, and an audio-cued visual search task. At the beginning of each task, a fixation cross in the center of the screen is presented for 5 seconds and can be used as a global baseline. After the last task, there is an additional measurement of a 5-second baseline. All tasks are presented in a fixed order, and in between the tasks, a short children’s cartoon (duration=30 s) is presented to maintain children’s attention and motivation. The overall duration of the battery is approximately 16 minutes. Prior to the task, we conduct a 6-point calibration. The source code of the tasks as a Python (Python Software Foundation) implementation can be found on the GitHub repository “locusmental_wp1_tasks” of [name].

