### Risk Assessment

We only include paradigms that are feasible in young children. This shall ensure a sufficient completion rate in preschoolers (>80%). The concurrent presentation of visual stimuli to maintain attention during the auditory oddball task may impede the SEPR. However, we recently showed in independent data that visual presentation during an auditory oddball task still induces distinct task-evoked pupillary responses.

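### As worded, the work package 1 exclusion rule can drop a child for one weak non-marker task yet keep a child with no data at all for that task

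*Protocol article*

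**What the plan says.** The rule stands in the missing-data paragraph at the end of Ethical Considerations, directly after the sentence on work package 1 feasibility: "Statistical analysis will exclude children that have per-task data validity rates of less than 50% or more than one missing task". The next sentence adds: "The auditory oddball task is a marker task that is required to be included in the statistical analysis". The paragraph then notes: "We established standardized procedures of pupillometry data preprocessing to address within-trial missing data due to inattention".

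The Battery Design overview for work package 1 states "The battery consists of 4 individual tasks", namely the auditory oddball as the primary task plus rapid sound sequences, a visual oddball and an audio-cued visual search. The tasks run in a fixed order. Elsewhere in Ethical Considerations, signs of acute distress in the child "will lead to termination of the assessment".

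The work package 1 power statement is "a power of *β*=.82 for 90 participants to detect a moderate stimulus effect (b=0.3) in the auditory oddball task (100 trials, 20% oddballs" (the article writes power as β). The work package 1 analysis plan uses intercorrelations among the measures to assemble the concise battery that the later work packages use.

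**The concern.** A quality rule should never rank a child with less usable data above a child with more. Followed as written, this one does. It contains no statement that a task below 50% counts as missing, so a low-validity task does not fall under the allowance of one missing task. It is a separate trigger that removes the whole child.

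Two things are at stake. First, usable data are lost: a child removed for a weak visual search also loses a valid auditory oddball recording, the task on which the work package 1 power rests. Second, inclusion would depend on whether a child stopped before a task or sat through it inattentively, which says nothing about the quality of the other three recordings. Because the article names inattention as a source of missing pupil data, the literal rule may remove less attentive children preferentially from the sample used to choose the battery.

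**Working it through.** **Step 1. The rule applied to two children.** Both have 90% validity in the auditory oddball, rapid sound sequences and visual oddball.

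| | Visual search | Task below 50%? | More than one task missing? | Literal result |
|---|---|---|---|---|
| Child A | 49% valid | yes | no | excluded |
| Child B | no data | no, task is missing | no, only one | kept |

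Child A has strictly more data and is dropped. The same happens with either of the other non-marker tasks. It does not happen with the auditory oddball: the marker-task sentence requires that task, so a child without it is not kept either.

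**Step 2. The plan's own figure.** The mixed-model variance components and alpha are not given, so the simulation cannot be rerun. Assuming two-sided 0.05 and reading b = 0.3 as a standardised within-child effect, power is Φ(0.3·√90 − 1.96) = Φ(0.886) = 0.81. Reading b as a correlation (Fisher z) gives Φ(0.3095·√87 − 1.96) = 0.82. The stated 0.82 for 90 children is consistent with either reading.

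**Step 3. Children kept.** Inputs from the article: 4 tasks, 90 children, auditory oddball required. Assumptions: each task is present but below 50% valid with probability p, independently, and no task is wholly missing. The article gives no value for p, so a range is shown.

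- Literal rule: (1−p)^4.
- Task-level rule (a low-validity task counts as missing; auditory oddball usable; at most one other task unusable): (1−p)·[(1−p)^3 + 3p(1−p)^2].

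At p = 10%: literal 0.9^4 = 0.656, so 59 of 90. Task-level 0.9·(0.729 + 0.243) = 0.875, so 79 of 90.

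| p | Literal: kept (of 90) | Approx. power | Task-level: kept (of 90) | Approx. power |
|---|---|---|---|---|
| 5% | 81.5% (73) | 0.73 | 94.3% (85) | 0.79 |
| 10% | 65.6% (59) | 0.64 | 87.5% (79) | 0.76 |
| 20% | 41.0% (37) | 0.44 | 71.7% (65) | 0.67 |

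Power uses the first approximation in Step 2 with the reduced number of children.

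**Step 4. Clustering.** If failures reflect a trait of the child, they concentrate in the same children. With a shared normal latent trait and an assumed between-task correlation r, at p = 10%:

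| r | Literal: kept (of 90) | Task-level: kept (of 90) | Gap, children |
|---|---|---|---|
| 0 | 65.6% (59) | 87.5% (79) | 19.7 |
| 0.3 | 70.5% (63) | 86.4% (78) | 14.4 |
| 0.6 | 76.1% (69) | 86.3% (78) | 9.2 |
| 0.8 | 80.7% (73) | 87.0% (78) | 5.6 |

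**Step 5. Selection.** In a simulation of the same model (r = 0.3 and 0.6, p from 5% to 20%), retained children average 0.20 to 0.58 SD below the mean on the trait that drives low validity under the literal rule, and 0.09 to 0.39 SD below it under the task-level rule. Both rules select; the literal one selects more. The trait and its correlation with validity are assumed.

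**The case against.** The strongest reply is that the sentence never says a single weak task is enough. 'Per-task' can be read as a task-by-task judgement in which a failed task is lost and the child goes only when more than one task, or the marker task, is lost. The rewording below may then only spell out what was meant. A condensed article may also leave the counting of validity to the full plan. In addition, gaze-contingent presentation in all four tasks is designed to limit low validity.

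Part of this stands. The task-by-task reading is possible, so the defect lies in the wording rather than in a proven intention. It does not dispose of the point: the article chose to state the rule, the stated unit is the child, and nothing in it says that a task below 50% becomes missing.

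Four stronger readings are tempting and are not supported:

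- *About 20 of 90 children will be lost.* That figure needs an undocumented 10% failure rate and independent failures. Independence also sits badly with the idea that restlessness drives the failures; clustering cuts the gap (Step 4).
- *The rule breaches the plan to "achieve a projected completion rate of over 80" percent.* That projection concerns finishing the tasks, not passing a quality filter. Child A finishes all four.
- *Restless children are shown to be selected out.* This is an inference. Any validity threshold selects to some degree, including the proposed one.
- *Work packages 2 and 3 share the defect.* The sentence follows the work package 1 text, and the article describes other missing-data methods for the longitudinal phase. No fault is shown there.

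**Conclusion.** The point holds in a limited form. For the three non-marker tasks the rule as worded is incoherent, and applied literally it discards usable data in the sample that selects the battery. That conclusion follows from the text alone and needs no assumed rate.

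The size is not known. Across assumed independent failure rates of 5% to 20%, the literal rule would keep roughly 12 to 28 fewer of 90 children than a task-level rule. At 10% the difference falls from about 20 to between 6 and 14 children when failures cluster at r = 0.3 to 0.8. Preferential loss of less attentive children is plausible but not documented. The rule should be corrected before the validation data are analysed, so that the choice between readings is not made with the results in view.

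**What to change.** Replace the exclusion sentence with: *A task with less than 50% valid data is set to missing for that child; a child is excluded only if the auditory oddball is missing under this rule or more than one task is missing.* Settle this before the work package 1 analysis, which the abstract plans for March 2026.

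Report the available characteristics of excluded and included children. Table 1 lists demographics and the two WPPSI subtests for objective 1; the CBCL and the irritability questionnaire are listed only from objective 2.1. The comparison therefore cannot test selection on irritability directly, and should not be presented as if it did.

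The cost is one sentence and one descriptive table, with no new data. Denominators will differ slightly between task-specific analyses and should be shown for each.

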### Task 3.2: LC-NE Functioning Mediates the Effect of Stress Responses on the Development of Transdiagnostic Psychopathology

#### Participants

Participants in this study will comprise a subsample of 5‐6-year-olds (n=160) at one randomly selected timepoint (T2 or T3) from the large longitudinal cohort (Task 3.1).

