#### Sample Size and Power

A power analysis using a bivariate latent growth curve model indicates a power of *β*=.82 for 160 participants to detect a moderate path coefficient (b=0.2) of cortisol reactivity on changes in psychopathology.

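### Task 3.2 excludes children with a missing hair or saliva sample from cortisol models that could keep them, risking attenuated paths and discarding mediator and outcome data

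*Protocol article*

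**What the plan says.** The missing-data rules are in the last paragraph of Ethical Considerations in the protocol article. For hair and saliva the rule is: "Missing bio samples will be addressed by case-wise exclusion in the specific subanalysis". For the rest of work package 3 the paragraph says that "the statistical framework of work package 3 includes LMM and structural equation modeling to handle intermittent missingness across time points". Questionnaire items are multiply imputed.

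The paragraph expects irritable or burdened children to drop out more often and labels this missing not at random. It answers with two safeguards. Pattern mixture models are to be used "to determine if the developmental trajectories of LC-NE functioning are biased by specific attrition patterns", and "Inverse Probability Weighting (IPW) in the longitudinal data analysis can be used to adjust for non-random attrition". Neither is tied to the cortisol analysis.

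Task 3.2 belongs to work package 3. Its Statistical Analysis Plan puts cortisol into a mediation model with LC-NE functioning and psychopathology. Its Sample Size and Power section reports power of .82 from a bivariate latent growth curve model "for 160 participants to detect a moderate path coefficient (b=0.2) of cortisol reactivity on changes in psychopathology". Samples are taken once, at T2 or T3. Under Measures, hair gives retrospective stress, and saliva before and after a social stress test gives the acute response.

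**The concern.** A child without a usable cortisol value may still have pupillometry and CBCL scores. A mediation or growth model fitted to all available data uses these for the path from LC-NE functioning to psychopathology. Case-wise exclusion discards them within Task 3.2.

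Exclusion can also bias the estimates if a missing sample is related to how the child is doing at the outcome wave. The protocol gives reasons to take this seriously:

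- An assessment is ended at signs of acute distress (Ethical Considerations), and salivary reactivity needs a second sample 30 to 40 minutes after the stress test (Task 3.2, Measures).
- Retention relies partly on phone and online contact (Task 3.1, Risk Assessment). That can deliver caregiver questionnaires but not a laboratory stress test.

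At stake are the estimates of the cortisol and mediator-to-outcome paths on which the Task 3.2 hypothesis rests.

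**Working it through.** **The plan's own figure.** The .82 comes from a Monte Carlo growth-curve model whose alpha, sidedness, loadings and variances are not given, so it cannot be rebuilt. Simple proxies for b = 0.2 and n = 160 (Fisher z; standardized slope) give 0.719 and 0.728 at two-sided 0.05, and 0.815 and 0.822 at one-sided 0.05. The point below does not depend on this figure.

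**Set-up of the illustration (all values assumed).** n = 160, 3000 replicates. P is baseline psychopathology, X cortisol, M LC-NE functioning, Y later psychopathology, and the e terms are independent standard normal errors:

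- X = 0.2·P + √0.96·e1
- M = 0.3·X + √0.91·e2
- Y = 0.55·P + 0.2·X + 0.2·M + 0.7·e3

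X is missing in 25 to 26%: completely at random, or with log-odds rising by 1 per unit of P, or by 1 per unit of Y. Case-wise regression is compared with maximum likelihood (ML) on all children, using P as an additional variable. Entries are mean estimate (empirical SE).

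| Missingness depends on | Path | No data missing | Case-wise | ML |
|---|---|---|---|---|
| nothing | X→Y given M | 0.310 (0.074) | 0.311 (0.086) | 0.312 (0.085) |
| nothing | M→Y given X | 0.200 (0.074) | 0.201 (0.086) | 0.199 (0.077) |
| P | X→Y given M | 0.311 (0.075) | 0.297 (0.087) | 0.310 (0.088) |
| P | M→Y given X | 0.201 (0.075) | 0.202 (0.086) | 0.201 (0.078) |
| P | X→Y given P | 0.261 (0.060) | 0.262 (0.070) | 0.262 (0.069) |
| Y | X→Y given M | 0.309 (0.075) | 0.277 (0.084) | 0.310 (0.090) |
| Y | M→Y given X | 0.201 (0.075) | 0.180 (0.083) | 0.201 (0.078) |
| Y | X→Y given P | 0.261 (0.059) | 0.242 (0.068) | 0.262 (0.070) |

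**Bias.**

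- When missingness depends on Y, the cortisol path shrinks by 1 − 0.277/0.309 = 10% and the mediator-to-outcome path by 1 − 0.180/0.201 = 10%. With baseline in the model the cortisol path shrinks by 1 − 0.242/0.261 = 7%.
- A second simulation with other assumed paths (true value 0.20 for both) gave 0.183 and 0.184 case-wise, a loss of about 8%, against 0.201 and 0.200 with ML.
- When missingness depends on P and P is in the model, case-wise exclusion is unbiased (0.262 against 0.261).

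**Precision.**

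- With values missing at random, the case-wise SE for M→Y is 0.086/0.077 = 1.12 times the ML value. The second simulation gave 0.077/0.069 = 1.12.
- In the same setting, the SE for the cortisol path is practically the same under both methods: 0.086 and 0.085 here, and 0.078 for both in the second simulation.

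**The case against.** The strongest reply is that this is a limited rule in one subanalysis. Exclusion applies only to the specific cortisol analysis, so LC-NE functioning and psychopathology are still related in all 300 children in Task 3.1. Nothing says that hair and saliva must both be present in one model, so a child lacking hair may stay in the saliva analysis. All of this stands, and it confines the loss to Task 3.2.

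A second reply is that the protocol's warning about selective loss concerns dropout, not attending children who lack a sample. That is correct. The warning reaches Task 3.2 only through children lost before T2 or T3, or followed remotely. Whether missing samples track outcome-wave psychopathology is plausible but not established.

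A third is that missing at random is not simply a weaker assumption. Complete-case regression remains valid when missingness depends on cortisol itself, and ML then loses its guarantee, although simulation showed little harm. The two assumptions are not nested, which is a reason to report both analyses.

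Two stronger readings are tempting and are not supported:

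- A reader might infer that the exclusion rule costs Task 3.2 its power. Scaling the stated .82 by √(n/160), with two-sided 0.05 assumed, gives .78 at 10% missing (n = 144), .73 at 20% (n = 128) and .67 at 30% (n = 112). But the .82 refers to the cortisol path, where ML recovers almost no precision. These figures show only that .82 presumes 160 children with salivary cortisol; changing the missing-data method would not bring that power back.
- A reader might infer that the 3 cm hair length lowers this power. The powered path is cortisol reactivity, which is measured in saliva.

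**Conclusion.** The point holds in limited form. The protocol fixes case-wise exclusion for models that can use incomplete children, and none of its other missing-data safeguards is stated for the cortisol models. If missingness depends on outcome-wave psychopathology, the cortisol and mediator-to-outcome paths are attenuated by about 8 to 10% at about 25% missing. With values missing at random, the standard error of the mediator-to-outcome path within Task 3.2 is about 12% larger than it need be (equivalently, ML cuts it by about 10%). These sizes rest on assumed path values and an assumed missing fraction, because the protocol gives no rate of missing samples. Exclusion is not biased under every mechanism: missingness that follows only modelled baseline scores does no harm. The issue is moderate, since it concerns one subanalysis and leaves the core longitudinal result of Task 3.1 intact.

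**What to change.** Replace the case-wise rule for Task 3.2 as follows:

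1. Fit the mediation and growth models by full-information maximum likelihood, or multiple imputation, in all children selected for Task 3.2. Use baseline CBCL, irritability, sex and the other cortisol measure as auxiliary variables.
2. Keep the case-wise analysis as a sensitivity analysis.
3. Extend the planned missing-not-at-random sensitivity analysis to the cortisol models, since neither primary approach covers that case in general.
4. State that the .82 presumes 160 children with salivary cortisol, so the power figure is not read as allowing for missing samples.

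The cost is analysis-plan wording and some added modelling. No extra data are needed: the auxiliary variables are already collected. The longitudinal study is scheduled to start in April 2026 and cortisol is sampled only at T2 or T3, so the rule can be changed before any of these data exist. The price is reliance on a missing-at-random assumption in the main analysis, which the two sensitivity analyses are there to test.
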